## Data analysis plan

### Adjustment for confounders

The coexistence of the two care approaches in the five participating countries may be considered a major strength of the present study. Yet, clustering in outcomes may be found within hospitals and countries; therefore, we will explore random effects for hospitals as part of mixed regression models.

### Analysis of clinical and social outcomes

Mixed effects models with an unstructured variance matrix will be used to assess differences in the primary outcome (rehospitalisation), and in the other clinical and social outcomes between the two groups. We will explore random effects for the hospitals or ‘specialisation’ and ‘personal continuity’ of care clusters within the hospital (in Germany, Belgium and Poland), and use fixed effects for the following covariates:
Age, gender, diagnostic group, whether or not a patient has been previously admitted, severity of illness at baseline, social situation (SIX score) and formal status of the patient at baseline.

We will check the selection bias by comparing data of our sample with the aggregate data for the total group of admitted patients during the same period.

Potential mediators of effectiveness may be: (1) the intensity of treatment, that is, sum of inpatient days and outpatient visits; (2) the experience of hospital care within the index admission, which has been shown to be predictive of better outcomes following discharge.^38^
^39^ A higher intensity of treatment or a better experience of hospital care may occur in either the ‘specialisation’ or the ‘personal continuity’ of care approach and be responsible for better outcomes.^21^
^38^ We will develop a mediation model^40^ in order to identify and explicate a potential effect of intensity of treatment and/or experience of hospital care during the index admission for assessing the effectiveness of the two approaches.^41^

Exploratory analyses to compare clinical outcomes, social outcomes and untoward events between the ‘specialisation’ and ‘personal continuity’ of care approaches will also be carried out on subgroups of patients defined by:
Age (younger or older than 40 years);Gender (males or females);Primary psychiatric diagnosis (F20–29 or F30–39 or F40–49);First or repeated admission;Socioeconomic situation (receiving state benefits due to low income or not);Migrant status (ie, country of residence different from country of birth or not);Presence of physical comorbidity/comorbidities for substance use, diabetes, cardiovascular diseases or not.

All subgroup analyses will be performed by including the relevant variables as interaction terms in the models.

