## Abstract

**Introduction:**

Mental healthcare organisation can either pursue *specialisation*, that is, distinct clinicians and teams for inpatient and outpatient care or *personal continuity of care*, that is, the same primary clinician for a patient across the two settings. Little systematic research has compared these approaches. Existing studies subject have serious methodological shortcomings. Yet, costly reorganisations of services have been carried out in different European countries, inconsistently aiming to achieve specialisation or personal continuity of care. More reliable evidence is required on whether specialisation or continuity of care is more effective and cost-effective, and whether this varies for different patient groups and contexts.

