### Sample size determination

The sample size for the quantitative study was calculated with the aim to detect a 5% difference in rates of re-admissions (ie proportion of patients re-hospitalised during the one year follow up) between the two care approaches from 27.5% to 32.5% with 80% power at the 5% significance level.

The sample size required for an individual-level comparison not considering clustering of outcomes within centres and hospital would be 2716 patients.

We calculated an average cluster size per hospital of 150 patients recruited over one year. Taking into account a 15% drop out rate, the average number per hospital of patients recruited and followed up will be 128. The variance inflation factor (or design effect, IF) is given by IF=1+(m−1)×ρ; where m=cluster size, and ρ=ICC (inter-cluster correlation coefficient). The ICC in a cluster with such a large number of patients is expected to be very small.^37^ With m=128 and ρ=0.007, IF is 1.90, and the adjusted sample size is N=5162 (1034 per country), requiring eight hospitals per country with an average number of 150 patients recruited per hospital, ie 1200 patients per country and 6000 overall.

We will carry out follow-up face-to-face interviews with a subsample of patients who will be 18–65 years of age. The patients will be stratified based on diagnostic group (ICD codes: F20–29, F30–39, F40–49)^27^ and on whether the index admission was their first one or they have had previous hospital admissions. We will aim to interview 30 patients per stratum, resulting in 360 patients per country (60×6 clusters) and an overall sample of 1800 patients (360×5 countries).

For the in-depth interviews, we will purposively select 40 patients and 13 clinicians in each country, resulting in a total sample of 200 patients and 65 clinicians.

Within the sample, there will be a mix of: (1) patients treated with ‘specialisation’ and ‘personal continuity’ of care approaches; (2) those who were rehospitalised during the follow-up and those who were not; and (3) patients with different diagnoses (F20–29, F30–39, F40–49).

Clinicians will be included taking into account: (1) the care approach (‘specialisation’ or ‘personal continuity’) adopted by the service they work within and (2) their qualification: psychiatrists, psychologists, nurses/social workers.

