## Discussion

COFI is a natural experiment which will overcome limitations of the currently available evidence:
It is a multicentre study carried out in countries with very different traditions, funding mechanisms and policies for mental healthcare. In all these countries, care approaches supporting either specialisation or personal continuity of care coexist. This will allow for comparisons to be made within a similar context and not be confounded by country-specific characteristics. The service arrangements supporting specialisation or personal continuity of care may vary substantially among the countries, which will make our findings more robust and increase their generalisability to other countries and contexts.It is powered to detect very small differences in clinical and social outcomes between the two care approaches assessed that are relevant from a policy decision-making point of view (eg, 5% in rates of rehospitalisation).A comprehensive range of outcomes will be assessed, encompassing clinical outcomes, social outcomes, safety of care indicators, patient satisfaction with services and cost-effectiveness.Care approaches supporting specialisation or personal continuity of care which are assessed in this study are already established as routine services and are not just pilot experimental services. This will be a methodological safeguard from the ‘novelty bias’ found in the existing literature in which the newly established approaches (either supporting specialisation or continuity of care) tend to have better outcomes than the traditional ones.^21^

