### Advantages of the adopted methodology

COFI will be the first natural experiment to compare different approaches to routine mental healthcare provision.

Natural experiments have a number of advantages over randomised controlled trials in health service research.^46–49^

From a practical point of view, the costs related to reorganisation of the mental healthcare services in multiple areas of a country for an experimental trial would not be sustainable or feasible. With a natural experiment design, a high number of patients can be recruited and the effectiveness of different care approaches can be assessed in different areas with no excess treatment costs.

From a scientific point of view, an assessment of routinely provided care avoids the ‘novelty bias’ related to the enthusiasm of patients and clinicians for a newly established way of receiving or providing care.^21^ Patients will be receiving and evaluating standard care instead of a new intervention.

The choice of the sites is very important for a natural experiment. The clinical sites recruited reflected a wide range of geographical areas. The five participating countries have both care approaches as part of their routine mental healthcare provision in different cities or areas of a different city; therefore, the comparison will not be biased by within-country variables. Potential clustering of outcomes will be explored considering random effects at a hospital level.

The countries selected for COFI offer a wide variety of traditions, policy models and funding mechanisms of mental healthcare. They are located in different areas of Europe and share commonalities in sociopolitical characteristics as well as practice and organisation of mental healthcare with non-included neighbouring countries. Therefore, it is expected that COFI findings can be generalisable to a larger number of countries in Europe than those included in the study.

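### The primary mixed model does not condition on country, so the protection from country confounding that the article claims is not secured by the analysis

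*Protocol article*

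**What the plan says.** Under Analysis of clinical and social outcomes, the fixed effects are "Age, gender, diagnostic group, whether or not a patient has been previously admitted, severity of illness at baseline, social situation (SIX score" (the bracket closes after the quoted words) and formal status at baseline: seven patient variables. The random effects are for hospitals or, in Germany, Belgium and Poland, for the approach clusters within a hospital. The secondary analysis of continuity as a continuum reuses the same covariates and a hospital random effect.

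The section on adjustment for confounders acknowledges that outcomes may cluster by country as well as by hospital, but responds only with hospital random effects. Potential challenges expects attrition to differ between countries and relies on the same structure to control for it. Study design says that practice, traditions, policies and funding differ significantly between the five countries.

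Against this, the Discussion states: "This will allow for comparisons to be made within a similar context and not be confounded by country-specific characteristics".

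Settings requires at least four hospitals per approach in each country. Under Procedures, approach is uniform within a hospital in the UK and Italy. In Belgium, Germany and Poland it depends on insurance or team decisions for individual patients.

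**The concern.** In the UK and Italy approach is constant within a hospital. In the other three countries, if the random unit is the approach cluster, it is constant within that unit too. The approach contrast is then made between units pooled over five countries. A random intercept treats the levels of those units as unrelated to approach; it does not turn the contrast into a within-country one.

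If countries differ in readmission rate and also in their share of units or patients under each approach, part of the country difference enters the approach effect. If shares are equal, the estimate is safe, but between-country variance goes into the hospital variance and widens the reported standard error. The study is non-randomised and targets a 5-point difference, so both matter for the primary result.

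This is more than detail left to a fuller plan. The article lists the covariates, reuses the list and rests a claim of protection on the design.

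**Working it through.** **1. The plan's own figures.** Inputs from Sample size determination: rates "from 27.5% to 32.5% with 80% power at the 5% significance level"; ICC 0.007; analysed cluster size 128.
- Two-sided test of two proportions: n0 = 1318 per arm. With continuity correction, n = (n0/4) × [1 + √(1 + 4/(n0 × 0.05))]² = 329.5 × (1 + √1.0607)² ≈ 1358 per arm, or 2716 in total, as stated.
- Design effect: 1 + 127 × 0.007 = 1.889. Then 2716 × 1.889 = 5131, or 2716 × 1.90 = 5160, against 5162 stated. The arithmetic is sound.
- At a 30% rate, an ICC of 0.007 means a between-hospital SD of √(0.007 × 0.30 × 0.70) = 0.038, or 3.8 points.

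**2. Assumption.** The documents give no between-country SD, so a range is used. At SD 5, five evenly spaced country rates around 30% are 23.7, 26.8, 30.0, 33.2 and 36.3% (30 + 5 × −1.265, −0.632, 0, 0.632, 1.265). Work is on the probability scale, without patient covariates.

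**3. Bias without country, SD 5.** Bias is the difference between the arms' average country deviations.
- Exact 4+4 with equal cluster sizes: 0.
- 7 clusters against 4 in the highest-rate country, 4+4 elsewhere: 5 × (3 × 1.265)/23 = 0.8 points.
- 4+4 everywhere, but cluster sizes running from 64 to 192 in opposite directions: 1.2 points.
- Splits 3/5, 3/5, 4/4, 5/3, 5/3: 5 × 2 × (2 × 1.897)/20 = 1.9 points.
- 8/4 in one extreme country and 4/8 in the other: 5 × 2 × (4 × 1.265)/24 = 2.1 points. Simulated type I error was 11.6% without country and 5.2% with it.

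At SD 3 these unbalanced layouts give 0.5 to 1.3 points.

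**4. Standard error and power, balanced layout.** Simulation of 40 hospitals of 128 (5120 analysed), 4+4 per country, within-country hospital SD 3.8 points, true difference 5 points, 4000 runs:

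| Country SD (points) | Mean SE without country | Power without | Mean SE with country | Power with |
|---|---|---|---|---|
| 0 | 1.75 | 80% | 1.74 | 81% |
| 3 | 1.94 | 75% | 1.75 | 82% |
| 5 | 2.27 | 64% | 1.74 | 81% |
| 7.5 | 2.78 | 41% | 1.73 | 81% |

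The actual spread of the estimates at SD 5 is 1.77 points with or without country; only the reported SE grows. Hand check: significance needs an estimate above 1.96 × 2.27 = 4.45, and Φ((5 − 4.45)/1.77) = Φ(0.31) = 62%, near the simulated 64%. The null rejection rate there is 1.6%, so the test is conservative. The design-effect formula gives lower power (71% at SD 3, 56% at SD 5), partly because it treats the inflated SE as true sampling error.

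**5. Dependence on the random structure.** Take country rates of 20 to 40% and suppose that every hospital in Belgium, Germany and Poland has both approaches, half each.
- Approach clusters as separate units: SE 2.41 without and 1.62 with country; power Φ(5/2.41 − 1.96) = 55% and Φ(5/1.62 − 1.96) = 87%.
- Hospital intercept with approach clusters nested in it: SE 1.80 and 1.56; power Φ(5/1.80 − 1.96) = 79% and Φ(5/1.56 − 1.96) = 89%.

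Most of the loss disappears under nesting, because the comparison in those three countries is then largely within hospital.

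**6. Dependence on the ICC.** If 0.007 is a within-country value, country variance comes on top, as in step 4. If it already includes country variance, the planned precision stands.

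**The case against.** The strongest reply is that the plan aims at four hospitals per approach in each country, and under exact balance the bias is zero and the estimate's true variability unchanged. That is correct. What remains is an inflated SE and a conservative test, a loss of power rather than a misleading estimate. But balance is not assured: four is a minimum, cluster sizes can differ, and three countries leave approach to insurance or team decisions. The documents permit imbalance; they do not show it.

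Second, the seven covariates may absorb part of any country difference, and the calculations omit them. This stands as a reason to read the figures as illustrations.

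Three stronger readings are tempting and not supported:
- A reader might infer that the trial is underpowered as planned. That needs a between-country SD and an ICC interpretation that the article does not give, and it depends on the random structure.
- A reader might build an uneven UK split from the figure of 11. That figure counts provider organisations (NHS Trusts), not hospitals, and no split by approach is given.
- A reader might say that a stated research question on context goes unanswered. The abstract's words, "whether this varies for different patient groups and contexts", describe evidence that is needed; the listed research questions and subgroups include no country comparison of effect.

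Finally, the sentence "therefore, the comparison will not be biased by within-country variables" concerns variables within countries, so it should not be counted as a second claim about confounding between countries.

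**Conclusion.** The point holds in a limited form. As written, the model conditions on country in neither its fixed nor its random part, so the Discussion's claim about country-specific characteristics rests on the design alone. The design delivers it only when approach shares are equal across countries.

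The possible bias is about 0.8 to 2.1 points of a 5-point target, given an assumed between-country SD of 5 points and the unbalanced layouts shown; under exact balance it is zero. The possible power loss under balance is from about 81% to 75% (SD 3) or 64% (SD 5) with 40 whole-hospital clusters. It is smaller with nested approach clusters, and there is none against plan if 0.007 is an overall ICC. The sample size arithmetic is not in error.

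**What to change.** Add country as a fixed effect with five levels (4 df) to the primary readmission model and to the other clinical, social and cost models, and keep the hospital random effect. In the simulations this removed the bias and held power at about 81% at the planned size, whatever the country differences.

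State in the sample size section whether the ICC of 0.007 is within-country or includes between-country variance.

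Optionally, report country-specific estimates or an approach-by-country interaction, labelled exploratory.

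The cost is analysis-plan wording and 4 degrees of freedom among more than 5000 analysed patients. No change to recruitment or data collection is needed.

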## Aims and objectives

COFI aims to compare outcomes, costs and experiences of ‘specialisation’ and ‘personal continuity’ of care approaches.

Readmission to hospital was chosen as the primary outcome of the study due to the high clinical relevance and impact on service costs. The validity of readmission rates as an outcome criterion for mental health service evaluation has been confirmed in previous studies.^23^
^24^

COFI will address the following research questions:
Primary research question
Do rates of rehospitalisation differ between the specialisation and personal continuity approaches?Clinical and social outcomes
Is there a difference in number of voluntary and compulsory rehospitalisations per patient and yearly inpatient bed days between the two approaches?Are untoward incidents (deaths, suicides, physical violence committed or experienced by patients) more frequent in either approach?What are the social outcomes, in terms of employment, accommodation, living situation, subjective quality of life and social contacts of patients treated by either approach?Costs of care:
What are the direct costs of care (ie, related to use of services) within each approach?Which approach is most cost-effective?Experience of care
What are treatment satisfaction and experiences of care provided by the two approaches and do they differ?

We will also carry out comparisons of the two approaches in subgroups of patients defined by age, gender, diagnosis, first admission, socioeconomic situation, migrant status and presence of physical comorbidities.

We hypothesise that:
The ‘specialisation approach’ may be more effective in providing specialised care for people with less complex and more specific mental health needs (eg, absence of comorbid disorders or social problems), who do not require coordination of different interventions.^1^
^12^The ‘personal continuity approach’, ensuring a stronger coordination of different interventions,^7^
^25^ may be more suited for treating patients who are affected by severely disabling mental health conditions (eg, schizophrenia) and comorbid physical illnesses, or those who have complex psychosocial needs such as patients with a low socioeconomic status, migrants and patients with comorbidities.

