### Baseline measures

At baseline, we will collect data on:
Sociodemographic characteristics: year of birth, gender, marital status, highest completed education level, country of birth;Social situation: employment, accommodation, living situation, friendships, self-reported benefits receipt due to low income;Psychiatric and non-psychiatric diagnoses according to the International Classification of Disease 10 (ICD-10);^27^ the primary clinical diagnosis is established from medical records or clinician’s report at discharge from hospital;Severity of illness, rated by treating psychiatrists by the Clinical Global Impression Scale (CGI);^28^Whether the current admission is the first one or not;Formal status at admission (involuntary/voluntary);Patient appraisal of inpatient care, as measured by the Client Assessment of Treatment (CAT).^29^

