#### Other clinical and social outcomes

*Clinical outcomes* including: (1) number of readmissions; (2) number of compulsory readmissions; (3) inpatient bed days, using an ad hoc schedule based on the Client Service Receipt Inventory.^30^*Social outcomes,* based on the SIX index,^31^ which captures*:* (1) employment (none; voluntary or protected or sheltered work; regular employment); (2) accommodation (homeless or 24 h supervised; sheltered or supported accommodation; independent accommodation); (3) living situation (living alone; living with a partner or family); (4) contacts with friends (not having met a friend within the past week; having met at least one friend in the past week).*Subjective quality of life*, measured by the Manchester Short Assessment of quality of life MANSA.^32^*Untoward incidents related to mental healthcare*, including: (a) deaths; (b) completed suicides; (c) serious assaults committed by patients; (d) physical violence experienced by patients; (e) suicide attempts; (f) serious side effects from pharmacological treatment requiring hospitalisation, as extracted from clinical records or obtained through phone interviews.*Social contacts,* measured as: (a) the total number of social contacts within the week preceding the assessment as reported by patients using an ad hoc instrument, adapted from the Social Network Schedule,^33^ and (b) whether or not they declare to have at least one close friend, using the specific item on the MANSA.^32^*Experienced discrimination,* measured as*:* (a) patient-reported episodes of discrimination because of mental illness, and (b) patient-reported avoidance of activities because of fear of discrimination, measured by ad hoc items.*Perceived socioeconomic status,* that is, patient self-rated standing in his/her own self-defined community and country, measured by the MacArthur Scale of Subjective Social Status.^34^
^35^

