#### Data collection at one-year follow-up

Clinical outcomes, employment, accommodation, living status, friendships, untoward events and indicators of care costs will be followed up for the *entire sample* via *medical records or telephone contact*.

To assess patients’ subjective quality of life, global social contacts, experienced and anticipated discrimination, perceived socioeconomic status, satisfaction with care, contacts with primary and secondary care professionals, and for patients’ experienced continuity of care we will randomly select a *subsample of patients, who will be interviewed face-to-face*.

Patients and clinicians interviewed for the *qualitative study* will be purposively selected from among those included in the entire sample. Selection criteria are reported in the following paragraph.

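### If the SIX domains are analysed as separate outcomes, adjusting for the baseline SIX score accounts only in part for each domain's own baseline value, although all four items are recorded

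*Protocol article*

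**What the plan says.** All references are to the protocol article.

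- **Analysis of clinical and social outcomes** prescribes mixed models for rehospitalisation and for the other clinical and social outcomes, with one list of fixed effects: age, gender, diagnostic group, previous admission, "severity of illness at baseline, social situation (SIX score) and formal status of the patient at baseline". No social item is listed separately.
- **Baseline measures** collects the items: "Social situation: employment, accommodation, living situation, friendships, self-reported benefits receipt due to low income".
- **Other clinical and social outcomes** bases the social outcomes on the SIX index and gives each component its own categories, for example "employment (none; voluntary or protected or sheltered work; regular employment" and, for friends, "not having met a friend within the past week; having met at least one friend in the past week".
- **Aims and objectives** puts the question by domain: "What are the social outcomes, in terms of employment, accommodation, living situation, subjective quality of life and social contacts".
- **Data collection at one-year follow-up** also names the domains one by one: "Clinical outcomes, employment, accommodation, living status, friendships, untoward events and indicators of care costs will be followed up for the" entire sample.

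**The concern.** A total is a weak stand-in for one of its parts. Someone living alone in sheltered work and someone living with family without work can have the same SIX score. A model for living situation that conditions on the score does not hold baseline living situation fixed.

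The study design gives this weight. Under Study design, the approach a patient receives follows geography, clinical decision and patient choice, or insurance. Any of these routes could differ by employment or household, and the same section stresses how much depends on confounder adjustment. A baseline difference on one item could then be reported as a social effect of the care approach. The plan would also forgo a strong predictor that is already in the data set.

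**Working it through.** **The plan's own figures.** A two-sided 5% test with 80% power for 27.5% against 32.5%, with continuity correction, needs 1358 per group, or 2716 in total, as stated. The design effect is 1 + 127 × 0.007 = 1.889, stated as 1.90. After 15% dropout, 6000 × 0.85 = 5100 patients are analysed. None of this changes below.

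**Assumptions.** The documents give no prevalences, item correlations or stability for the SIX items, so everything from here is assumed. The SIX score is taken as the sum of the four items. At baseline 60% live with others, 35% have any work, 70% have met a friend and 80% live in independent accommodation, with items independent. A follow-up item keeps its baseline value with probability s and is otherwise redrawn, so s is also the correlation between baseline and follow-up.

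**False difference in living situation.** Let δ be the baseline gap on the item, D the gap in the score, and q the item's variance divided by the score's variance. With no true effect:

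- unadjusted: s × δ
- adjusted for the score: s × (δ − q × D)
- adjusted for the items: 0

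Simulated correlations of follow-up living situation with the score and with its own baseline are 0.20 and 0.50 at s = 0.5, so q = (0.20/0.50)² = 0.16. Take δ = 5 points.

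| s | Unadjusted | Score, only this item differs (D = 5) | Score, another item offsets (D = 0) | Items |
|---|---|---|---|---|
| 0.5 | 2.5 | 0.5 × (5 − 0.8) = 2.1 | 2.5 | about 0 |
| 0.7 | 3.5 | 0.7 × 4.2 = 2.9 | 3.5 | about 0 |
| 0.9 | 4.5 | 0.9 × 4.2 = 3.8 | 4.5 | about 0 |

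Simulation agrees to within about 0.2 points. The score removes about one sixth of the confounding, or none when another item offsets it.

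**Regular employment.** Employment makes up more of the score, so the score does better for it. The simulation used 5120 patients, 30% in regular employment at baseline, 60% or 80% of those still employed at one year, 8% of the others newly employed, latent item correlation 0 or 0.3, baseline shifts of 0.2 SD and no true effect. False differences in points:

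| Baseline pattern | Unadjusted | SIX score | Own baseline |
|---|---|---|---|
| Only employment differs (about 7 to 8 points) | 3.6 to 5.6 | 1.5 to 2.9 | about 0 |
| All items shift the same way | 3.7 to 5.6 | −1.8 to −0.8 | about 0 |
| Other items shift the opposite way | 3.6 to 5.3 | 4.6 to 6.7 | about 0 |
| Only the other items differ | −0.4 to 0.1 | −3.9 to −2.4 | about 0 |

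Own-baseline adjustment lay between −0.3 and +0.1 throughout.

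**Precision.** With m = 128 and ρ = 0.007, the design effect splits into 0.993 within and 128 × 0.007 = 0.896 between clusters, so 0.896/1.889 = 47% of the variance is between clusters. If the baseline covariate explains only patient-level variance, with correlation r:

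SE = 2 × √(p(1 − p)) × √((0.993 × (1 − r²) + 0.896)/5100), and power = Φ(0.05/SE − 1.96).

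For living situation at s = 0.5, the score (r = 0.20) gives SE 0.0187 and power 76%. The own item (r = 0.50) gives SE 0.0176 and power 81%.

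| Outcome, s | r with score | Power, score | Power, own item |
|---|---|---|---|
| Living situation, 0.5 | 0.20 | 76% | 81% |
| Living situation, 0.7 | 0.28 | 77% | 87% |
| Any work, 0.5 | 0.33 | 80% | 83% |
| Any work, 0.7 | 0.46 | 82% | 89% |

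Applying (1 − r²) to the whole variance, clusters included, would give larger gains (living situation 77% to 86% and 79% to 96%). That supposes that the item also explains the between-hospital part, which nothing in the protocol supports. The ICC itself was set for readmission.

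**The case against.** The strongest objection is that the protocol never says the domains are modelled one by one. It describes the social outcomes as based on the SIX index. If the outcome is the SIX total, the listed score is that outcome's own baseline and the plan is right. This stands, and it makes the point conditional. Separate analysis is still the likelier reading, because the research question and the follow-up section both name the domains individually.

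A second objection is that outcome-specific covariates are usually left to the analysis plan, which is not shown. But the article does more than stay silent. It assigns one list to every social outcome, and someone following it would fit the weaker model.

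A reader might infer that the social models adjust for nothing but the score, or that each item's baseline is missing altogether. The documents support neither. Six other covariates are listed, though none is an item baseline, and each item enters the score in diluted form. Nor is it general that most of an imbalance survives: for employment alone the score roughly halves it, and when all items shift together the remainder is smaller still, with its sign reversed. The large residuals need items that move in opposite directions, and the protocol gives no sign that they do.

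It is also tempting to extend the point to the subsample outcomes on close friends and social contacts. Baseline measures lists neither of those instruments, so the baseline friendship item would be a proxy and not their own baseline.

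**Conclusion.** The point holds as a conditional improvement. For any SIX domain analysed separately, the listed score is a poorer covariate than the domain's own baseline value, which the study already holds. With a 5-point baseline gap in living situation and independent items, about 2 to 4 points of false difference would remain, against about 0 with item adjustment. The residual can be smaller or larger depending on how the other items differ. The gain in power is about 3 to 10 points. These sizes rest on assumed prevalences, stability and imbalance, and they leave out the other covariates. The primary outcome, the sample size and an analysis of the SIX total are unaffected.

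**What to change.** In Analysis of clinical and social outcomes, state that each model for a single SIX domain (employment, accommodation, living situation, friend contact) enters the four baseline SIX items as separate fixed effects, including the outcome's own baseline category, in place of the SIX score. Keep the score where the follow-up SIX total is the outcome and in all other models. It would help to say in the same place whether the domains, the total or both are analysed.

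The cost is a sentence or two. No new data are needed, and the sample size does not change. Two three-level and two binary items use 2 + 2 + 1 + 1 = 6 degrees of freedom instead of 1, so five more in about 5100 patients. The domain models would no longer share the primary model's exact covariate list, and sparse lower accommodation categories may need merging.
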